## Introduction

### Background

The management of brain metastases presents a significant challenge in oncology. Whole brain radiation therapy (WBRT) is widely given to improve neurological symptoms, stop brain metastasis progression and possibly prolong survival. Unfortunately, neurocognitive functional decline is reported in a significant number of patients who undergo WBRT at rates of 31–57% at 3 months and 48–89% at 1 year [1].

The hippocampus plays a key role in learning, memory and cognitive function [2–4]. The significance of hippocampi radiation in clinical studies is emerging. Gondi et al. showed that a dose of > 7.3Gy to at least 40% of the hippocampus resulted in a significant decline in delayed recall in adult brain cancer patients [5].

A recent phase 3 trial, NRG-CC001, randomised 518 patients to Hippocampal avoidance-WBRT (HA-WBRT) against standard WBRT. Cognitive endpoints were measured using a test battery of Hopkins Verbal Learning Test-Revised (HVLT-R), Controlled Oral Word Association, and Trail Making Test (TMT) Part A & B. At a median follow-up for alive patients of 7.9 months, a significant reduction in cognitive failure risk was noted (HR, 0.76; *P* = 0.03) in the HA-WBRT arm. This difference was most significant in the 4-month TMT Part B scores and the 6-month HVLT-R score. The median overall survival (OS) and progression free survival (PFS) did not differ and there was no increase in hippocampal relapses. However notably, OS and PFS in the HA-WBRT arm were poor at 6.3 months and 5.0 months respectively [6].

This trial introduced HA-WBRT as a new standard option in patients with multiple brain metastases and good prognosis. However, some clinicians would still favour the use of Stereotactic Radiosurgery (SRS) over HA-WBRT in patients with low volume brain metastases. The reasons could possibly be better cognitive sparing or tumoral control due to the higher ablative doses used in SRS. Several trials are underway comparing the use of HA-WBRT against SRS (ClinicalTrials.gov identifier: NCT03550391, NCT03075072 and NCT04277403).

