#### Secondary endpoints

Intracranial Progression▪ Target lesion or distal brain lesion▪ Symptomatic or asymptomatic brain lesion
PFSOS▪ Neurological or non-neurological death▪ Cancer or non-cancer related deathCognitive Function▪ HVLT-R (immediate recall, delayed recall, and total recall)▪ Colour Trail Test (CTT) – a language-free version of the TMTQuality of Life (QoL)▪ Functional Assessment of Cancer Therapy with Brain Subscale (FACT-BR)▪ Euro QOL – 5 Dimension – 5 Level (EQ-5D-5L)Activities of Daily Living (ADL)▪ Barthel Index of ADLsToxicity▪ Scored using Common Terminology Criteria for Adverse Events (CTCAE) ver5.0 criteria▪ Presence of radiation necrosis (asymptomatic or symptomatic)

All time points will be taken from the time of randomisation to event. If response assessment of the target lesion(s) is uncertain or equivocal, this should be reassessed by a multi-disciplinary team for clarification. When needed, this may be followed up with advanced imaging or histology.

Cognitive function, ADL and QoL will be assessed using patient-directed questionnaires that have been validated, available in local languages and used in the trials mentioned earlier for ease of comparison. These tests are optional but encouraged for all patients and will be conducted by a trained physician or clinical research associate at specified time points (Table 3). The total duration of the combined test is estimated to be 30 min. In the analysis of cognitive function, ADL and QoL, each patient will serve as his/her own control. The test results at each follow-up (post-treatment) time point will be compared to the baseline (pre-treatment) test result.

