## Statistical methods

### Statistical analysis plans

Efficacy analyses will be performed using the intention-to-treat principle. Per-protocol analyses may be performed as secondary analyses. Safety analyses will include all patients who started treatment and will be performed according to the actual treatment received.

The primary endpoint, time to target lesion progression, will be defined as the time from randomisation to target lesion progression. Patients who pass away before documented target lesion progression will be censored at the last brain imaging assessment. Time to target lesion progression will be compared between the 2 treatment groups using a 2-sided log-rank test.

Time to intracranial progression, time to symptomatic brain progression, progression-free survival and overall survival will be defined as the time from randomisation to intracranial progression, symptomatic brain progression, overall progression and death from any cause respectively. All time-to-event endpoints will be summarized using the Kaplan-Meier method. Treatment arms will be compared using log-rank tests and Cox proportional hazards models, adjusting for the stratification variable (number of brain metastases). Other prognostic variables such as histology, ECOG status and disease-specific GPA class may also be included in the Cox models.

Adverse events will be recorded according to CTCAE version 5.0 and summarised by treatment arm.

Cognitive test (HVLT-R and CTT) scores will be standardised based on published norms: (Patient value – Published-norm mean value) ÷ Published-norm standard deviation value. Cognitive deterioration will be defined as a decline of at least 1 SD in score from baseline. FACT-BR scores will be transformed to a 0- to 100- point scale. A 10-point decrease will be considered clinically significant. Deterioration in functional independence will be defined as a decline of at least 10% in the Barthel ADL index from baseline.

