The proportions of patients with cognitive deterioration, QoL deterioration and functional independence deterioration will be compared between treatment arms using Fisher’s exact test. A sensitivity analysis will be conducted assuming patients who had not completed the neurocognitive assessment or had passed away prior to the assessment time-point, had cognitive deterioration. Change from baseline values will be compared using 2-sample t-tests and repeated measures linear regression, adjusting for the stratification variable (number of brain metastases).

All analyses will use a 2-sided 0.05 level of significance. There will be no adjustment for multiple comparisons.

There is no planned interim analysis for this study.

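### Fisher's exact test for the deterioration proportions runs at about 2.0 to 3.5% rather than 5%, and an equally exact test would recover the lost power at no cost

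*Protocol article*

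**What the plan says.** Under Statistical analysis plans, the Protocol article defines three binary deterioration outcomes. For cognition, "Cognitive deterioration will be defined as a decline of at least 1 SD in score from baseline"; for FACT-BR the threshold is 10 points on a 0 to 100 scale; for the Barthel index it is a 10% decline. The proportions reaching these thresholds "will be compared between treatment arms using Fisher’s exact test". The level is fixed for everything: "All analyses will use a 2-sided 0.05 level of significance", and "There will be no adjustment for multiple comparisons".

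Two further provisions in the same section bear on the point. The underlying scores are also analysed as continuous: "Change from baseline values will be compared using 2-sample t-tests and repeated measures linear regression, adjusting for the stratification variable". A sensitivity analysis for cognition assumes that patients who "had not completed the neurocognitive assessment or had passed away prior to the assessment time-point, had cognitive deterioration".

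The article gives no expected deterioration rate, effect size or power for any of these outcomes.

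**The concern.** Cognition, quality of life and function are where an added boost dose could do harm, and the stated hypothesis is better control while these are maintained. Fisher's test conditions on the total number of deteriorations. With a few dozen patients per arm, few p-values are attainable, so its real false-positive rate falls well below the nominal one. The trial would then accept a higher chance of missing a true difference without needing to. In a trial this small, a non-significant comparison is easily read as preservation, so unnecessary loss of power matters even for secondary endpoints.

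**Working it through.** **Inputs.** From the Sample size section: 30 evaluable per arm, inflated for 40% non-evaluable. This reproduces: 60 / (1 − 0.40) = 100, or 50 per arm enrolled. The questionnaires are optional, so 20 per arm is added as an assumed low case. Two-sided alpha is 0.05 and allocation 1:1. Deterioration rates are not given; 20 to 50% is assumed. There is no power figure for these endpoints to reproduce.

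**Step 1: true level of Fisher's test.** With n per arm, a common rate π and binomial probabilities b,

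level(π) = Σ over x, y of b(x; n, π) · b(y; n, π) · 1[Fisher p(x, y) ≤ 0.05].

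Full enumeration gives:

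| n per arm | π = 20% | 30% | 40% | 50% |
|---|---|---|---|---|
| 20 | 2.3% | 2.5% | 2.4% | 2.0% |
| 30 | 2.2% | 2.6% | 2.6% | 2.7% |
| 50 | 2.8% | 3.1% | 3.2% | 3.5% |

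At π = 10% it is lower still: 0.9% at 30 per arm and 1.8% at 50.

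**Step 2: Boschloo's test.** Use the two-sided Fisher p-value only to rank the tables. Reject when it is at or below c, the largest cutoff for which the level, maximised over every π, stays at or below 0.05. Because Fisher's own region (c = 0.05) already satisfies that limit, c is at least 0.05. Boschloo's region therefore contains Fisher's, and its power cannot be lower. Enumeration over a fine grid of π gives:

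| n per arm | cutoff c | maximum level |
|---|---|---|
| 20 | 0.091 | 4.6% |
| 30 | 0.069 | 4.7% |
| 50 | 0.069 | 4.9% |

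As an example, 8/30 versus 16/30 has a Fisher p of 0.064. It is not significant under the plan but is significant at 0.05 under Boschloo's test.

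**Step 3: power.** The same sum, with π₁ in one arm and π₂ in the other:

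| Rates | n per arm | Fisher | Boschloo | Gain (points) |
|---|---|---|---|---|
| 30% v 50% | 20 | 16% | 22% | 6 |
| 30% v 50% | 30 | 26% | 34% | 8 |
| 30% v 50% | 50 | 46% | 53% | 7 |
| 30% v 60% | 20 | 35% | 45% | 10 |
| 30% v 60% | 30 | 56% | 65% | 9 |
| 30% v 60% | 50 | 83% | 85% | 3 |

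Gains are computed before rounding. At 20, 30 and 50 per arm, over six pairs of rates, the gain was about 3 to 10 points. The smallest gain in any setting checked was 1.4 points (25 per arm, 40% v 60%).

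**Step 4: why not simply use Pearson's chi-square?** It has slightly more power (35% for 30% v 50% at 30 per arm) but does not guarantee the level: its exact size reached 6.5% at 25 per arm with π = 50%.

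**The case against.** The strongest reply is that Fisher's test is a standard, valid small-sample choice, that these are secondary endpoints with no power target, and that the plan does not rest on it alone. All of that stands. The section also plans t-tests and a repeated-measures regression that uses all visits and the stratification factor. In simulations with a 0.6 to 0.8 SD mean difference, the month-6 t-test had 43 to 89% power where month-6 Fisher had 22 to 60%. With no multiplicity adjustment planned, one could also welcome a conservative test. But the amount of conservatism is an accident of the rate and the sample size, not a chosen control of error.

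Four stronger readings are tempting, and the article does not support them.

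- **That the 0.05 level is contradicted.** A test with a true level of 2.0 to 3.5% respects a 0.05 limit.
- **That the plan has about half the power of a time-to-deterioration analysis.** The article gives no rate, effect size or time course. Under assumed scenarios, the ratio of single-visit Fisher power to log-rank power was about 0.4 to 0.7 for persistent or early constant effects, but about 1 when the difference grows late. Most of any gap comes from using one visit, not from Fisher's test.
- **That patients who deteriorate and then die are simply ignored.** For cognition, the sensitivity analysis counts them. It does not extend to quality of life or function.
- **That results cannot be compared with the cited phase 3 trial, where "a significant reduction in cognitive failure risk was noted (HR, 0.76".** The instruments were chosen because they were "used in the trials mentioned earlier for ease of comparison", which concerns questionnaires, not test statistics. The Background also reports that trial's 4- and 6-month differences, and its cognitive battery differs from this one.

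**Conclusion.** The point holds as a limited efficiency weakness in secondary analyses, not as an error or contradiction. Fisher's test uses roughly 2.0 to 3.5% of the 5% allowed at 20 to 50 evaluable per arm with rates of 20 to 50%. Against an equally exact alternative it gives up mostly 3 to 10 percentage points of power. These figures assume equal arms and a single two-arm comparison of proportions. They do not depend on whether the proportion is taken visit by visit (the likely reading) or as ever having deteriorated, except through the rates and numbers that result. The gain is modest: at 30 per arm, a 30% v 50% difference would still be missed about two times in three (1 − 0.34 = 0.66), so a non-significant result would remain weak evidence that function was preserved.

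**What to change.** In Statistical analysis plans, replace Fisher's exact test with Boschloo's unconditional exact test at two-sided 0.05. State that tables are ordered by the two-sided Fisher p-value, since the guarantee of never losing power depends on that ordering. Report each difference in proportions with a 95% confidence interval, so the reader can see what size of harm is not excluded.

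Keep the t-tests, the repeated-measures regression and the sensitivity analysis unchanged.

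Optionally, add time from randomisation to first deterioration as a supportive analysis, with death as a competing event and a cause-specific hazard ratio. This answers a different question from the proportions, and transient declines would count as events unless confirmation is required.

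The cost is one or two sentences of analysis text, settled before between-arm results are seen. No new data, visits or patients are needed.

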### Sample size

Assuming a 6-month target lesion control rate of 50% in the HA-WBRT arm, we will need 60 subjects (30 per arm) to detect a hazard ratio of 0.27 [9] between the 2 arms with 80% power using a 2-sided log-rank test at 5% significance level. A hazard ratio of 0.27 means the 6-month target lesion control rate in the HA-SIB-WBRT arm is expected to be 83%. These calculations assume that subjects will be followed up till target lesion progression, or for a minimum of 6 months. Assuming a 40% non-evaluable rate, an estimated total sample size of 100 subjects will be required.

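### Change scores for cognition, quality of life and ADL are compared without the baseline score as a covariate, which gives up some precision in these secondary analyses

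*Protocol article*

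**What the plan says.** The protocol article, under Statistical analysis plans, sets out two kinds of analysis for the cognitive, quality-of-life and ADL outcomes.

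- **Deterioration.** Thresholds are fixed (1 SD on the cognitive tests, 10 points on FACT-BR, 10% on the Barthel index), and the proportions who deteriorate "will be compared between treatment arms using Fisher’s exact test".
- **Mean change.** "Change from baseline values will be compared using 2-sample t-tests and repeated measures linear regression, adjusting for the stratification variable", named in brackets as the number of brain metastases.

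The role of the baseline score is described under Secondary endpoints: "In the analysis of cognitive function, ADL and QoL, each patient will serve as his/her own control", and "The test results at each follow-up (post-treatment) time point will be compared to the baseline (pre-treatment) test result". For the cognitive tests there is one further step: "Cognitive test (HVLT-R and CTT) scores will be standardised based on published norms". That places a score against a reference population; it does not adjust the arm comparison for the patient's own starting level.

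Nowhere is the baseline score named as a covariate. The only allowance for further prognostic variables is for the Cox models of the time-to-event endpoints.

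**The concern.** Analysing raw change treats follow-up as rising one unit for each unit of baseline. When the true slope is below 1, patients who start high tend to fall and those who start low tend to rise. Change is then correlated with baseline, and that avoidable variation stays in the arm comparison. A chance difference in baseline scores between arms also carries over into the estimated difference in change.

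Randomisation is simple within two strata of metastasis number, so nothing in it balances baseline cognition, quality of life or ADL. Effects on cognition and patient-reported outcomes are part of the stated purpose of the trial. The tests are optional and the trial is small, so the numbers analysed may be low and precision matters. The adjustment set is stated in the article, so this concerns a stated choice and not a detail left to an analysis plan that is not shown.

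**Working it through.** **The plan's own figure.** No SD, correlation or power is given for the change scores. The only sample size is for the primary endpoint: "we will need 60 subjects (30 per arm) to detect a hazard ratio of 0.27", raised to 100 for 40% non-evaluable. This reproduces closely:

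- 0.5^0.27 = 0.829, matching the stated 83%.
- The Schoenfeld formula needs 18.3, so 19, events. The mean 6-month event probability is (0.50 + 0.171)/2 = 0.335, and 19/0.335 = 56.7, or 29 per arm (58 against the stated 60).
- 60/(1 - 0.40) = 100.

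The point does not touch these figures. Thirty per arm is borrowed below only as a plausible number with scores, and 50 per arm is the upper limit.

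**Assumptions not in the documents.** Baseline SD s0, follow-up SD s1, and correlation rho.

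**Variance per patient.**

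- Change score: s0^2 + s1^2 - 2 rho s0 s1
- Baseline-adjusted: s1^2 (1 - rho^2)
- Difference between them: (s0 - rho s1)^2, which is never negative

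With s0 = s1 = 1 these become 2(1 - rho) and 1 - rho^2, so the ratio of adjusted to change score is (1 + rho)/2. Effective size is 30 divided by that ratio. Power is for a true difference of 0.5 SD with 30 per arm, 2-sided 0.05, normal approximation.

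| rho | Var, change | Var, adjusted | Ratio | Effective n per arm | Power, change | Power, adjusted |
|---|---|---|---|---|---|---|
| 0.5 | 1.00 | 0.75 | 0.75 | 40.0 | 0.491 | 0.609 |
| 0.6 | 0.80 | 0.64 | 0.80 | 37.5 | 0.581 | 0.677 |
| 0.7 | 0.60 | 0.51 | 0.85 | 35.3 | 0.705 | 0.774 |
| 0.8 | 0.40 | 0.36 | 0.90 | 33.3 | 0.865 | 0.898 |
| 0.9 | 0.20 | 0.19 | 0.95 | 31.6 | 0.991 | 0.993 |

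**Unequal SDs.** The gain depends on s0/s1 as well as rho.

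- s0/s1 = 0.8, rho = 0.6: change 0.64 + 1 - 0.96 = 0.68; adjusted 1 - 0.36 = 0.64; ratio 0.94.
- s0/s1 = 0.7, rho = 0.7: change 0.49 + 1 - 0.98 = 0.51; adjusted 1 - 0.49 = 0.51; ratio 1.00, no gain.

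**Chance imbalance.** The baseline difference D between arms has SD sqrt(2/n): 0.26 SD at 30 per arm and 0.20 SD at 50. An imbalance beyond 0.25 SD in either direction has probability 33% and 21% respectively. Given D, the error in the change-score difference is -(1 - rho s1/s0)D, which is -(1 - rho)D with equal SDs. For D = 0.25 SD it is -0.125 SD at rho 0.5, -0.075 SD at rho 0.7 and -0.025 SD at rho 0.9.

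**Check by simulation** (20,000 trials, 30 per arm, equal SDs). The variance ratio was 0.77 at rho 0.5 and 0.86 at rho 0.7, slightly above the formula because the slope is estimated. Averaged over all trials, the change-score difference was centred on zero (-0.0008 and -0.0001 SD). In trials with an imbalance of 0.2 to 0.3 SD its mean error was -0.129 and -0.079 SD, against about -0.006 SD after adjustment.

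**The case against.** The strongest reply is that nothing here is invalid. Over all randomisations the change-score difference is unbiased and its test is sound. A reader might infer from the imbalance argument that the estimate is biased. The documents do not support that: allocation is randomised, and the error exists only conditional on the baseline difference observed. This part of the reply stands in full.

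Second, the size is uncertain. The (1 + rho)/2 ratio needs equal SDs, and a narrower spread at baseline is plausible. Eligibility excludes dementia, moderate-severe depression, ECOG above 2 and symptomatic metastases limiting ADLs, and the Barthel index may sit near its ceiling at entry. The gain could then be small or nil for some outcomes. This also stands. It limits the benefit without favouring the stated method, because in large samples adjustment does not lose precision and in small ones it costs little more than the estimation of a slope.

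Third, much is already planned. The repeated measures model is there, so the restriction of a t-test to patients seen at one visit is not the whole analysis. The Fisher comparisons, with a sensitivity analysis that counts death or non-completion as cognitive deterioration, give another route by which harm could show. What remains is the missing covariate and the unadjusted t-tests.

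A reader might also infer that about half the patients will have died by 6 months, making every lost unit of precision critical. The nearest figure is a 6.3-month median survival in the HA-WBRT arm of an earlier phase 3 trial. This trial requires a life expectancy of at least 6 months, so that figure cannot simply be carried over.

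Finally, a model with baseline as one of the repeated outcomes and a common baseline mean would also solve the problem. The article, however, describes a comparison of change values, and its named adjustment set does not include baseline.

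**Conclusion.** The point holds as one of efficiency in secondary analyses. The stated comparison of change scores is valid, but it leaves out a covariate that must be collected anyway to compute change. With equal SDs and rho between 0.5 and 0.9, adjustment lowers the variance of the arm difference by 25% to 5%, equivalent to 33% to 5% more patients (2/(1 + rho) - 1). It also largely removes the error that follows from a chance baseline imbalance. The benefit is material at rho of 0.5 to 0.7, small at 0.8 or above, and nil where the baseline SD equals rho times the follow-up SD. Confidence is high that the covariate is absent from the stated set and that adding it is sound; it is only moderate on the size, because the article gives neither SDs nor correlations. The primary endpoint, its log-rank test, the sample size of 100 and the deterioration comparisons do not depend on this.

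**What to change.** In Statistical analysis plans, make the repeated measures model the main analysis of the continuous HVLT-R, CTT, FACT-BR, EQ-5D-5L and Barthel scores. Include arm, visit, arm-by-visit, the outcome's own baseline score, baseline-by-visit, and the stratification variable. Report the arm difference with its 95% CI at each visit, in place of the unadjusted 2-sample t-tests. Leave the Fisher comparisons and their sensitivity analysis as they are.

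The cost is a change of wording, best made before the outcome data are compared by arm. It needs no new data, patients or visits.

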## Oversight and monitoring

### Safety

There is no independent Data Safety Monitoring Committee for this study. Any ≥Grade 3 serious adverse events must be reviewed by the co-investigators to determine if this toxicity is treatment related. All serious treatment related toxicities must be reported to the institutional review board (IRB). If any ≥Grade 4 toxicities are noted, the study will stop for review of safety before continuation, cessation or amendment of trial.

The principal investigator and co-investigators will be responsible for monitoring patient recruitment, toxicities, observed results and the evaluation of data quality. This will be done every 3 months.

